### Inclusion Criteria

Youths will be eligible to participate if they meet the following criteria: (1) 14-17 years of age with the cognitive ability to understand and comprehend the assenting process; (2) HIV-positive and aware of their status, that is, disclosed to; (3) receiving ART and care from one of the participating clinics; and (4) living within a family, including with extended family members (not in institutions). We will identify youths with depressive symptoms by administering the Patient Health Questionnaire-9 (PHQ-9) [61], which has been validated in rural settings in Uganda [62,63]. Youth scoring ≥10 on the PHQ-9 will be considered for enrollment. Youths will be excluded if they do not meet the inclusion criteria above or are unable to understand the informed consent process, or inability or unwillingness to commit to study completion. Health care providers will be recruited if they are working directly with youths living with HIV at their clinics and agree to participate in the study.

### Participant Recruitment and Consent

Procedures tested in our previous and ongoing studies in the study region will be used [59,60,64,65]. Specifically, participants will be identified and recruited from health clinics that are currently collaborating with ICHAD and Reach the Youth in the study region. A list of eligible participants will be created from medical records. Health care providers will present the study to adult caregivers of eligible youth during adolescent clinic days. These are scheduled days when youths visit clinics for ART refills, counseling, and treatment check-ins. If caregivers are interested, verbal consent to be contacted by a research staff (who will be onsite) will be requested. Next, the adult caregiver and the youth will separately provide consent or assent for the youth to be screened. Youths who meet the inclusion criteria and their caregivers (separately) will undergo an informed consent process to participate in the study. The consent and assent forms will clearly state that the youth can withdraw from the study at any time, for any reason, with no explanation, and will not be penalized. Caregivers will sign the consent form consenting for their children to participate. Youths will sign an assent form. If either the youth or the caregiver refuses to participate, the youth will not be enrolled. Health care providers will go through the same process and sign a standard consent form.

### Sample Tacking and Retention

The project will take place in a highly stable region of Uganda, where geographical moves are rare. In addition to recommendations garnered by focus group discussion participants in aim 1, we will use several practices to increase retention. During our interviews, youths will be asked to provide details of contacts, including telephone number, and names, addresses, and contact information for 3 people who will always know how to reach them. Participants will be reminded that if the research team were to contact the people listed, the team would never discuss any details about the participant’s involvement in the study. A phone call reminder will be made prior to each assessment. Our team has effectively used these methods in all our research projects, resulting in very low attrition [66-69]. We will keep careful records for those who drop out of the study and test for attrition bias based on data collected prior to study dropout. To the extent that such bias is present, we will limit generalizations accordingly, or, where possible, introduce statistical adjustments to address bias. Retention efforts will be periodically reassessed, reviewing best practices to reduce attrition.

### Ethics Approval

We obtained approval for all study procedures from the Uganda Virus Research Institute Research Ethics Committee (Ref: GC/127/919) on August 29, 2022, Washington University in St. Louis Institutional Review Board (IRB; 202209115) on October 06, 2022, and from the Uganda National Council for Science and Technology (Ref: SS1442ES) on November 15, 2022. The study is registered in the Clinical trials.gov database (Identifier: NCT05965245).

### Description of the Study Conditions

In phase 2 of the study, participants will be randomized to 2 conditions (100 youths per condition): a waitlist control condition or the Suubi-Mhealth condition, as detailed below.

#### Waitlist Control Condition

A waitlist control condition method will be used [70]. Participants will be randomly assigned to a waitlist and will receive the Suubi-Mhealth intervention after the active treatment group. In addition, participants will receive a smartphone without the Suubi-Mhealth app at the same time as the intervention group.

#### Suubi-Mhealth Treatment Condition

##### Overview

Participants in this condition will receive the Suubi-Mhealth intervention, with the specific components described below. All modules will be available in text, video, and audio format. All app content will be available in Luganda local language.

##### Evidence-Based Multimedia Psychoeducational Content to Reinforce Treatment Plans

Educational content will be provided within Suubi-Mhealth and broken into 20 modules. Users will be provided access for 2 months and will be instructed to review ≥2 modules per week. The research team has aligned Suubi-Mhealth content with state-of-the-science recommendations for CBT for ART adherence and depression as applied to HIV medication adherence [33]. In addition, the research team has implemented a group- CBT intervention to address depression and HIV-related stigma among adolescents [59,71]. This manualized intervention, developed with close consultations with mental health experts in the region, will be adapted into Suubi-Mhealth content. Core instruction will include psychoeducation on the interplay between HIV and depression; minimizing cognitive distortions related to ART adherence, stigma, and depression; challenging negative automatic thoughts; analysis and development of behavioral skills; reducing environmental stressors; creating support and helping communicate concerns adaptively and clearly; and problem-solving [37,38].

##### Safety Plan

To ensure safety while using the app, participants will be informed that the social networking center is informational only and not equipped for managing crises. Messages from users will be reviewed by a trained member of the research team within 24 hours. If signs of an imminent crisis are detected, a supervisor will send a crisis referral, make a report, and notify the parent so that no user waits longer than 24 hours to receive support. Emergency contact information will be shown in the corner of the survey page for all assessments.

##### Goal Setting and Self-Monitoring Features to Enable Self-Management

Our previous mHealth participants have indicated their desire for a goal-setting feature within an app, and studies of mobile apps have demonstrated that goal-setting, self-tracking, and monitoring features are essential to facilitate self-management skills and sustain user engagement [72,73]. With this in mind, there will be an ability to set goals and monitor symptoms of depression over time within Suubi-Mhealth. Rewards within an app have been shown to motivate and sustain healthy behaviors [74]. Our rewards feature will be used to inspire completing psychoeducation content and attaining goals by awarding digital “trophies” for participants who successfully meet a goal or reach a milestone (eg, complete a module on how to challenge negative automatic thoughts).

##### Clinical Dashboard to Monitor Participants’ Use of Suubi-Mhealth

A clinical management dashboard will make it efficient for the research team to input participant data and monitor participant use of the app and assessment responses.

### Data Collection

Data will be obtained through an eligibility screening checklist, computer-assisted, interviewer-administered structured questionnaires, focus group discussions, and semistructured in-depth interviews. All assessments will take place at the clinic, participant’s home, or ICHAD’s field offices in Masaka. Assessments will be conducted by trained Ugandan Research Assistants.

### Qualitative Assessments

Focus group discussions and semistructured interviews will be conducted. In phase 1, we will conduct 4 separate 60-minute in-person focus group discussions (6-8 youths each) and 2 focus group discussions for health care providers. Participants will be asked about impressions of expert-suggested content and design and their own suggested components for Suubi-Mhealth that could be of greatest utility for unique needs. They will also be asked for input regarding methods to increase participation and retention for follow-up assessments. All focus groups will be conducted in Luganda, will last approximately 1-hour and will be held in a private location at each clinic. In addition, we will conduct a 30-minute semistructured qualitative interview with each participant to further explore their experiences with Suubi-Mhealth, including perceived benefits and challenges of participation, and suggested modifications to improve specific components of the intervention. Complications or technical glitches with the app, and how it fared in regard to its ease of understanding, helpfulness, intuitive flow, presentation, and pacing will also be assessed. We will also conduct in-depth interviews with research staff who will be moderating the app.

In phase 2, we will conduct semistructured in-depth interviews with 30 participants upon completion of the intervention to explore their experiences with the intervention as well as barriers and facilitators to implementation and participation. Participants will be purposefully sampled [75], using a combination of high- and low-app users, that is, those in the upper and lower quartiles of engagement with the app (15 participants per group), to take part in a 30-minute semistructured qualitative interview. Interviews will focus on participants’ experience with Suubi-Mhealth and how it fared in regard to its ease of understanding, helpfulness for supporting ART adherence and depression, intuitive flow, presentation, pacing, and the likelihood that they would recommend this intervention to a peer. Reactions to specific content and suggestions for improvement will also be assessed. We will additionally perform in vivo observations in which participants actively use the tool during the interviews to more directly observe challenges to use and implementation.

### Quantitative Assessments

Quantitative assessments will be administered as follows. In phase 1, interviewer-administered quantitative assessments will be collected at 2 months post intervention to examine the usability characteristics and engagement with Suubi-Mhealth. To assess usability characteristics, we will administer a modified version of the 19-item USE (Usefulness, Satisfaction, and Ease of Use) questionnaire to measure usability characteristics of Suubi-Mhealth [76,77]. The USE will ask participants to rate the ease of use and learning (ie, efficiency), usefulness (ie, technical effectiveness), and likability (ie, satisfaction) of Suubi-Mhealth on a 7-point Likert scale (with 1= strongly disagree and 7= strongly agree).

To assess engagement with Suubi-Mhealth, automatically captured data within the app platform will be used to measure app engagement for each participant, including (1) the number of modules completed, (2) the number of messages sent, (3) the number of times self-monitoring and goal-setting features used, (4) the number of times logged into the app, (5) the time spent in the app once logged in, and (6) the time difference between app log-ins.

In phase 2, assessments will be completed at baseline and at 1, 2, and 6 months post intervention to evaluate whether participants’ ART adherence and self-reports on symptoms of depression, mental health functioning and physical health, and quality of life and stigma improve with access to Suubi-Mhealth and whether improvements remain consistent over time. The measures to be used are provided in Table 1 below.

**Table 1 table1:** Phase 2 assessment measures.

Variable	Measures
Demographics	Sociodemographic questionnaire
Depressive symptoms	Patient Health Questionnaire-9 (PHQ-9) [61] and Brief Symptom Index (BSI) [78]
Physical health	The Medical Outcomes Study HIV Health Survey (MOS-HIV) [79]
Quality of life	Pediatric Quality of Life Inventory (PedsQL 4.0) [80,81]
HIV shame	Shame questionnaire [82,83]
HIV stigma	Berger HIV Stigma Scale [84]
Social support	The Multidimensional Scale of Perceived Social Support [85] and Social Support Behavior Scale (SS-B) [86]
ART^a^ adherence	Viral load; self-reports [87]
Intervention feedback	In-depth interviews

^a^ART: antiretroviral therapy.

### Data Analysis Procedures and Milestones

#### Phase 1, Aim 1: to Develop and Iteratively Refine an Intervention Protocol for Suubi-Mhealth Based on Formative Work

##### Overview

We will conduct 4 focus group discussions, each with 6-8 youths (N=32), and 2 groups with health providers (n=16) for feedback on proposed intervention content and methods to increase participation and retention. Focus groups will be audio-recorded and transcribed verbatim. Transcripts will be translated into English and imported into Dedoose to assist with qualitative data management and coding. Inductive thematic analysis of focus group transcripts will be conducted by 2 research team members using the 6 steps described by Braun and Clarke [88] (getting familiar with the data, creating initial codes, looking for themes, reviewing and refining themes, defining and naming themes, and producing the report).

##### Milestone for Aim 1

We will have garnered input from youths and health care providers about the proposed Suubi-Mhealth content, features, and design. Participants will provide feedback on additional suggested components for Suubi-Mhealth that could be of the greatest utility for their unique needs. Suubi-Mhealth will be refined accordingly including its technical aspects, features to add or edit, and content updates or revisions. Participants will also be asked for input regarding methods to increase participation and retention for follow-up assessments. The study design and methods will incorporate feedback received from participants. Specifically, the research team will incorporate relevant suggested content and features into the Suubi-Mhealth intervention protocol before testing.

#### Phase 1, Aim 2: to Explore the Usability, Feasibility, and Acceptability of Suubi-Mhealth in a Small Sample to Inform Subsequent Refinement for the Larger Phase

##### Overview

Following the integration of input and feedback from focus groups to update and refine Suubi-Mhealth (phase 1, aim 1), we will β test Suubi-Mhealth among 30 youths. This is within the range of sample sizes for other pilot tests of digital therapeutics [77,89], and the suggested number of participants for pilot studies [90]. This sample size should be sufficient to explore the usability of and engagement with Suubi-Mhealth and for data saturation for qualitative interviews [91]. Participants will be instructed to use all features of Suubi-Mhealth for 2 months for the purpose of this β test. Two months for β testing is similar in length to other pilot tests for mental health apps [92,93], and will allow sufficient time for participants to engage with as many of the modules and features as they would like. Upon completion, we will garner feedback from each participant via mixed methods exploratory design in order to inform further enhancements of Suubi-Mhealth prior to the RCT (phase 2)*.* We will conduct both quantitative assessments to examine the utility and usability of the Suubi-Mhealth and qualitative interviews to explore participants’ experiences with the app.

##### Analysis Procedures

Quantitative assessments will be recorded using Qualtrics, an electronic data capture system. The data will be exported into the Statistical Analysis System for analysis. App usability will be examined using descriptive measures (mean, SD, median, and range) on the efficiency, technical effectiveness, and satisfaction components of the USE questionnaire. Descriptive statistics will also be used to describe engagement with the app (eg, the median number of logins and time spent in the app). Qualitative data will be analyzed in Dedoose following the same procedures provided in aim 1 above.

##### Adaptation and Feedback Integration Process

We will use procedures similar to those in our other studies for adapting mental health interventions based on target user feedback [94]. Specifically, participants’ feedback gathered from content and usability testing, as well as from experiences obtained during in-depth interviews, will be incorporated into the app based on the level of importance and feasibility including cost. The research team, including the research staff overseeing the app and selected youth, will go over each module to make sure that relevant revisions have been incorporated. Together, the research team will review and approve the adapted content and design before launching phase 2.

##### Milestone for Aim 2

Participants will have, on average, engaged with 75% or more of the mobile app modules and will express enthusiasm over its potential to be a supportive tool. Participants will score Suubi-Mhealth as having high ease of use and learning (ie, efficiency), usefulness (ie, technical effectiveness), and likability (ie, satisfaction). Participants’ provided feedback will be integrated into the app design.

#### Phase 2, Aim 1: to Pilot-Test the Preliminary Impact of Suubi-Mhealth

##### Overview

During phase 2, participants will be randomized to the intervention condition to engage with the Suubi-Mhealth app or the control condition (waitlist control group) to receive the app after the active intervention period. Assessments will be completed at baseline and at 1 month, 2 months, and 6 months post intervention to evaluate whether participants’ self-reports on symptoms of depression, ART adherence, mental health functioning, quality of life, and stigma improve with access to Suubi-Mhealth and whether improvements remain consistent over time.

Participants will also complete the USE measure to assess acceptability and usability, as well as in-depth interviews to explore their experiences with the intervention.

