**Methods:**

Youths will be eligible to participate in the study if they are (1) 14-17 years of age, (2) HIV-positive and aware of their status, (3) receiving care and ART from one of the participating clinics, and (4) living within a family. The study will be conducted in 2 phases. In phase 1, we will conduct focus group discussions with youths and health care providers, for feedback on the proposed intervention content and methods, and explore the feasibility and acceptability of the intervention. In phase II, we will pilot-test the preliminary impact of the intervention on reducing depression and improving ART adherence. Assessments will be conducted at baseline, 1-, 2-, and 6-months post intervention completion.

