##### Mixed-Effect Models

The principal strategy to examine primary and secondary outcomes over time between the Suubi-Mhealth group and the control group will be the use of linear mixed models and generalized linear mixed models, including a random intercept to allow for the correlation of within-participant measurements over time. Models will include the fixed effects of the intervention group (Suubi-Mhealth vs control), time, and group-by-time interaction. Effect sizes and 95% CIs will be reported.

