##### Sample Size and Power

The primary outcome in aim 1 is whether depression decreases between baseline and postintervention initiation. This is calculated from the depression score change between these 2 time points and categorized as yes versus no. The intracluster correlation for clinics is assumed to be 0.093 and the rate of depression decrease in the control group is 5% [95]. Given our total sample (N=200, 100 youths per condition, 5 clinics per condition), we expect to achieve at least 80% power to detect a rate difference of depression decrease when the rate of depression decrease in the intervention group is 40% and the 2-sided significance level of the test is .05.

##### Milestone for Phase 2, Aim 1

Successful completion of a parallel-group RCT to test the feasibility, acceptability, and preliminary efficacy of Suubi-Mhealth*.* Participants will not experience any adverse events. Participants will have engaged with Suubi-Mhealth daily for 2 months and engaged with at least 75% or more of the modules.

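### Waitlist access to the app is not tied to the follow-up schedule, so the 6-month contrast between arms, and on one reading every follow-up contrast, may compare early with delayed access

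*Protocol article*

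**What the plan says.** **When controls get the app.** The Phase 2, Aim 1 overview describes "the control condition (waitlist control group) to receive the app after the active intervention period". The Waitlist Control Condition section says that these participants "will receive the Suubi-Mhealth intervention after the active treatment group". Neither gives a date or refers to an assessment visit.

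**How long the active period is.** The section on psychoeducational content states: "Users will be provided access for 2 months".

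**When outcomes are measured.** The abstract's Methods paragraph says: "Assessments will be conducted at baseline, 1-, 2-, and 6-months post intervention completion". The Phase 2, Aim 1 overview says "Assessments will be completed at baseline and at 1 month, 2 months, and 6 months post intervention", without saying whether the clock starts at the beginning or the end of the intervention. Quantitative Assessments is equally open. Sample Size and Power defines the primary outcome as "whether depression decreases between baseline and postintervention initiation", with no month attached.

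**What is compared.** Primary analyses are by intention to treat. Under Mixed-Effect Models: "Models will include the fixed effects of the intervention group (Suubi-Mhealth vs control), time, and group-by-time interaction". The stated purpose of the repeated assessments includes finding out "whether improvements remain consistent over time".

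**The concern.** A waitlist arm is an untreated comparator only until it is treated. Once controls have the app, an intention-to-treat comparison of the original arms estimates the effect of having it earlier rather than later. If the app works and controls catch up, that contrast moves toward zero. A group-by-time interaction would then show the arms converging, which could be misread as a benefit that fades in the intervention arm. The durability question would also have no untreated group to be judged against.

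The article gives an earliest point for release of the waitlist, two incompatible hints about the visit clock, and a model that spans all visits with no restriction or term for crossover. Following it as written can yield a late between-arm result that does not answer the question asked.

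**Working it through.** **Step 1: timeline, in months from the start of app access.** Access ends at month 2, which is the earliest point at which the text lets controls receive the app.

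| Visit clock | Where it comes from | Follow-up visits | Visits after the earliest release |
|---|---|---|---|
| From completion | Abstract, Methods | 2+1 = 3, 2+2 = 4, 2+6 = 8 | all three |
| From initiation | implied by the outcome definition in Sample Size and Power | 1, 2, 6 | the last only |

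The 6-month visit falls after the earliest release on both clocks. On the initiation clock the month-2 visit sits at the boundary; it is clean if done before release.

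**Step 2: reproduce the plan's power.** Inputs from Sample Size and Power: 5% versus 40% with a decrease in depression, intracluster correlation 0.093, 100 youths and 5 clinics per arm (20 per clinic if equal), two-sided 0.05.

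- Design effect = 1 + (20 − 1) × 0.093 = 2.767; effective n = 100 / 2.767 = 36.1 per arm.
- Unpooled standard error = √[2.767 × (0.05×0.95 + 0.40×0.60) / 100] = √0.007955 = 0.0892.
- Difference / standard error = 0.35 / 0.0892 = 3.92.
- Power: 93% (t on 10 − 2 = 8 df), 98% (unpooled z), 96% (pooled z).

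The stated figure of at least 80% therefore holds. It rests on a 5% control rate, which is a rate for controls who have not had the app.

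**Step 3: the same endpoint at an exposed visit.** Let f be the share of the 35-point effect that controls have gained by then. The control rate becomes 5% + f × 35 points, and the intervention rate is kept at 40%. The article gives no f, so it is varied. The standard error is recomputed for each row by the formula in Step 2.

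| f | Control rate | Difference (points) | Difference / SE | Power (t, 8 df) |
|---|---|---|---|---|
| 0 | 5% | 35 | 3.92 | 93% |
| 0.10 | 8.5% | 31.5 | 3.36 | 84% |
| 0.25 | 13.75% | 26.25 | 2.64 | 64% |
| 0.50 | 22.5% | 17.5 | 1.63 | 30% |
| 0.75 | 31.25% | 8.75 | 0.78 | 11% |
| 1 | 40% | 0 | 0 | 5% (alpha) |

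The loss of power reflects a shrinking difference, so the point estimate is affected as well: at f = 0.50 the estimated difference is half of what it would be against untreated controls.

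**The case against.** The strongest reply is that the word *after* sets an earliest point and not a date. Both descriptions of the waitlist are compatible with holding the app back until the active group has finished follow-up. The 2-month figure limits users' access and does not schedule the waitlist. A condensed article may also leave the release date to the full protocol. This stands as far as it goes: crossover at month 2 is the plain reading, not a stated fact, and if release follows the 6-month visit the problem disappears. But both sections tie access to the end of active treatment, neither mentions the last assessment, and the article itself uses two different anchors for timing.

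A reader might infer that the trial has no clean comparison at all. The article does not support that. It requires both the completion clock and release soon after month 2. On the initiation clock, months 1 and 2 precede release and the primary comparison can be intact.

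A reader might also average the arm effect over the three follow-ups and report one diluted figure. The article plans no such average: the model has a group-by-time interaction, so the effect may differ by visit, and the primary outcome is defined between two time points.

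Finally, this is a pilot of preliminary impact, and a late immediate-versus-delayed comparison is an accepted trade-off in waitlist designs. That is fair, provided the late comparison is labelled as such. Here it is presented as evidence on whether improvement lasts.

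**Conclusion.** The point holds in conditional form. The timing of waitlist access is not reconciled with the assessment schedule. On the plain reading, the 6-month between-arm contrast compares early with delayed access under either clock. Whether the 1- and 2-month contrasts are also exposed depends on which clock applies, and the article points both ways.

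The size cannot be fixed from the article. At an exposed visit, power runs from about 93% with no catch-up, through 64% at one quarter and 30% at one half, down to the significance level at full catch-up. These figures assume equal clinic sizes, the article's binary endpoint applied at that visit, an intervention rate still at 40%, and an unpooled t test on 8 df. The power statement itself is not wrong; it applies at a visit where controls have not yet had the app.

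**What to change.** 1. Reconcile the abstract, Waitlist Control Condition, Quantitative Assessments, the Phase 2, Aim 1 overview, and Sample Size and Power on two matters: the date from which visits are counted, and when waitlist participants receive the app relative to each visit. Count visits in both arms from one common date, such as clinic randomisation or baseline.
2. Limit the primary between-arm contrast to visits before waitlist participants receive the app, and name the visit to which the primary outcome refers.
3. Report any later visit either as an immediate-versus-delayed comparison, labelled so, or as within-arm follow-up. Word the durability question to match.

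The cost is wording in the protocol and the analysis plan; no extra participants are needed. The 6-month between-arm efficacy claim is lost unless the reconciled text shows that controls do not yet have the app at that visit. If the reconciled text confirms the completion clock together with release at the end of the active period, no scheduled follow-up would qualify under item 2, so the reconciliation has to come first.
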